## Abstract

**Background:**

Chiropractic care is commonly used to treat musculoskeletal conditions and has been endorsed by clinical practice guidelines as being evidence-based and cost-effective for the treatment of patients with low back pain. Gaps in the literature exist regarding the physiological outcomes of chiropractic treatment. Previous pilot work has indicated the possibility of improvements in response time following the application of chiropractic treatment. However, it is unknown whether or not chiropractic treatment is able to improve reaction and response times in specific populations of interest. One such population is the U.S. military special operation forces’ (SOF) personnel.

**Methods:**

This study is a randomized controlled trial of 120 asymptomatic volunteer SOF personnel. All participants are examined by a study doctor of chiropractic (DC) for eligibility prior to randomization. The participants are randomly allocated to either a treatment group receiving four treatments of chiropractic manipulative therapy (CMT) over 2 weeks or to a wait-list control group. The wait-list group does not receive any treatment but has assessments at the same time interval as the treatment group. The outcome measures are simple reaction times for dominant hand and dominant foot, choice reaction time with prompts calling for either hand or either foot, response time using Fitts’ law tasks for small movements involving eye-hand coordination, and brief whole body movements using the t-wall, a commercially available product. At the first visit, all five tests are completed so that participants can familiarize themselves with the equipment and protocol. Assessments at the second and the final visits are used for data analysis.

**Discussion:**

SOF personnel are highly motivated and extremely physically fit individuals whose occupation requires reaction times that are as quick as possible during the course of their assigned duties. A goal of CMT is to maximize the functionality and integration of the neuromusculoskeletal systems. Therefore, chiropractic treatment may be able to optimize the capacity of the numerous components of those systems, resulting in improved reaction time. The objective of this study is to test the hypothesis that CMT improves reaction and response times in asymptomatic SOF personnel.

**Trial registration:**

ClinicalTrials.gov, NCT02168153. Registered on 12 June 2014.

## Background

Chiropractic manipulative therapy (CMT) is generally used to treat musculoskeletal conditions, with a focus on spinal health. Spinal manipulation (SM) is the primary chiropractic intervention [1]. Multiple clinical practice guidelines have endorsed CMT as being evidence-based and cost-effective for the treatment of patients with acute, subacute, and chronic low back pain (LBP) [2–4]. These guidelines are based upon randomized controlled trials (RCTs) that demonstrate SM to be a conservative and effective approach for the treatment of LBP [5–8]. In the U.S., between 7 and 14 % of U.S. adults see a doctor of chiropractic (DC) annually, resulting in more than 190 million patient visits and there are more than 70,000 licensed DCs [9–12]. CMT receives high patient approval ratings in studies done to assess patient satisfaction [13–16]. In addition to private practice, DCs treat patients in a variety of settings including multidisciplinary health care organizations such as Veterans Health Affairs and military treatment facilities [17, 18]. Currently, DCs provide treatment in 65 military treatment facilities both within and outside the U.S. [19].

SM is used by professional sports teams to enhance player performance. Currently, there is some preliminary evidence that CMT may have a positive effect on both reaction time and movement time [20, 21]. Kelly et al. found that participants demonstrated a significant improvement in a complex reaction time task after receiving CMT [22]. Both Smith et al. [23] and Passmore et al. [24] reported that hand and head movements in response to visual stimuli were completed more quickly after participants had received CMT. Daligadu et al. reported that 10 volunteers with subclinical neck pain were able to complete specified sequences of button presses on a keypad more quickly after receiving CMT [25]. No adverse events (AEs) were reported in any of these studies.

One group that relies heavily on peak physical performance is special operation forces (SOF) of the U.S. military. Enhanced performance is critical for this population as they encounter dangerous situations. Split-second delays in response times to threats may mean the difference between life and death. It is for this reason that the Office of the Congressionally Directed Medical Research Programs issued a Program Announcement that led to the Defense Health Program Chiropractic Clinical Trial Award (W81XWH-11-2-0107) to, in part, “assess military readiness by evaluating pre-post differences in reflexes and reaction times following chiropractic treatment using a pre-post interventional cohort trial in members of Special Operation Forces.” In response, the objective of this study is to test the hypothesis that CMT improves the reaction and response times of these highly motivated and extremely physically fit individuals.

## Methods

### Overview

This study is a RCT measuring reaction and response times in 120 volunteer SOF personnel at the Blanchfield Army Community Hospital, Fort Campbell, KY, USA. Following a first visit for screening and practicing the five biomechanical tests to be used in assessments, participants are randomly allocated to either a treatment group or to a wait-list control group. Beginning within a week of their first visit, those in the treatment group receive four CMTs over 2 weeks. The first of two assessments consisting of five biomechanical tests is made during their second visit, along with their first CMT. The second assessment is made during their final visit, along with their fourth CMT. In both of those visits with assessments, some of the biomechanical testing is performed before the CMT and some performed after. Participants in the wait-list control group do not receive any treatment but complete the two biomechanical assessments at the same time intervals as those in the treatment group. A flow chart of the study is shown in Fig. 1. Following their involvement in the study, those in the wait-list control group are offered the opportunity to receive four CMTs.

**Fig. 1 Fig1:**
[figure not shown]
Assessment of Chiropractic Treatment, part 2 (ACT 2) study flow chart and timeline

### Trial organization

This RCT is being conducted at Fort Campbell, KY because it has a population of SOF personnel as well as an established chiropractic clinic. The space to conduct the study, including the equipment used in the biomechanical tests, is housed within the facility used by the Chiropractic Clinic at Blanchfield Army Community Hospital. The CMT for this study is provided by two DCs, each with more than 10 years of clinical experience, practicing under the auspices of clinical guidelines established by the Department of Defense (DoD) and MedCom.

The investigators forming the research team for this study are from three collaborating institutions: the RAND Corporation, Palmer Center for Chiropractic Research (PCCR), and the Samueli Institute. Grants administration is managed by the RAND Corporation including the financial aspects and Institutional Review Board (IRB) issues of the grant award. It also ensures that the program officer at the DoD receives the required deliverables. The Samueli Institute ensures that the study complies with those entities that regulate the conduct of human subjects’ clinical research within the DoD, which include the U.S. Army Medical Research and Material Command Human Research Protection Office and the Army’s Clinical Investigation Regulatory Office. The Samueli Institute also provides advice concerning the general processes associated with the conduct of research within the military community.

Investigators from the PCCR are responsible for developing, implementing and managing the RCT at Fort Campbell. The investigators at Fort Campbell include: the site project manager (PM), two DCs (one of whom serves as site project investigator (PI)), and a physician medical monitor. The site PM is responsible for day-to-day trial implementation including recruitment and enrollment of trial participants, administration of a practice session and two biomechanical assessments of each participant, ensuring that each participant completes all phases of the study within the prescribed time windows, recording AEs, and maintaining all site-level trial documentation. The site PI oversees site administration including IRB issues, monitors study progress, conducts study evaluation and CMTs and ensures that all study procedures are conducted according to the protocol.

The lead PM at the PCCR oversees trial operations at Fort Campbell, acts as a liaison between trial coinvestigators, and ensures protocol adherence and fidelity. AEs are reviewed and monitored by a clinician at the PCCR. The project committee, consisting of all PCCR personnel involved in the study, meets weekly to review progress and resolve any issues that may arise. Any potential changes to the protocol are discussed in these meetings. Action steps are determined for obtaining approval from the three IRBs and informing all relevant study personnel.

The Submission Tracking and Reporting System (STaRS) used in this RCT is a comprehensive web application developed by the PCCR with a dual purpose of collecting outcome assessments for study participants and serving as a secure electronic data capture and clinical trial management system. STaRS includes modules for confirmation of participant eligibility, biomechanical assessment file exchange, data collection of study participant’s outcome assessments, and real-time reports for study management.

### Data and Safety Monitoring Committee

A Data and Safety Monitoring Committee (DSMC) provides oversight for this study. All DSMC members are independent of Palmer College of Chiropractic. Responsibilities of the DSMC are: (1) to ensure the overall safety of participants in clinical trials conducted by PCCR investigators by protecting participants from avoidable harm, and (2) to advise the DoD and the Expert Advisory Board regarding the scientific and ethical conduct of this RCT.

The DSMC reviews reports biannually. Should an AE occur, the DSMC evaluates the related data to protect the safety of study participants. If necessary, DSMC members make recommendations to the PIs and the DoD regarding continuation, termination, or other modifications of the RCT.

### Recruitment procedures

#### Initial contact

Flyers describing the study are placed in SOF facilities at Fort Campbell. SOF unit commanders and health care providers assigned to deliver care to SOF help to identify appropriate methods for dissemination of information concerning this study to their personnel. Quarterly presentations about the study are made in the language school on post as each new class begins. SOF soldiers who are interested contact the site PM by phone or email. The PM briefly describes the nature and extent of the study and asks basic screening questions. If the potential participant is still interested and appears to be eligible, the site PM arranges a preliminary visit to the study location for more extensive screening in a private setting.

### Visit 1

At the first visit, the site PM explains the study in detail utilizing the study flow chart and describing the specific activities of each visit. The site PM then goes over the Informed Consent Document with each participant and gives them a chance to read it and a Health Insurance Portability and Accountability Act (HIPAA) Compliance Document. The site PM is available to answer any questions they may have about either document or any aspect of the study. If the individual still desires to enroll in the study, the participant signs both documents and the site PM signs as a witness. The site PM then conducts an interview in which basic demographic information is obtained. The PM also screens the participant based on nonclinically obtained eligibility criteria. Those criteria are shown in Table 1 along with a rationale for why each was included. The PM enters the participant information directly into the STaRS system. Once preliminary eligibility is determined, the participant logs into the secure web application participant database (STaRS) and completes a demographic information form, a health care utilization and medication use form, and the Patient Reported Outcomes Measurement Information System (PROMIS)-29 Health Survey. After the questionnaires are completed, one of the two DCs in the chiropractic clinic reviews the participant’s medical records and conducts a physical examination. If no contraindications to chiropractic care are identified by the DC, the participant is referred back to the PM to complete the remainder of the visit. Participants with identified contraindications to CMT are ineligible to participate and referred to an appropriate provider if other care is needed. Those who are eligible are given an orientation of the five biomechanical tests. The orientation includes three videos, each approximately 2 or 3 min long, which demonstrate and narrate each of the five different tests..They show each test being performed and explain how the timing is measured for each one. Then the participant practices the five different biomechanical tests, repeating each one three times. The instructional videos were created to ensure that each study participant would receive standardized instructions. An appointment is then made for visit 2 within a week of visit 1.

**Table 1 Tab1:** Eligibility criteria

Inclusion criteria	Rationale
Minimum age of 20 years	Minimum age of SOF personnel
Written informed consent	Must be able to understand and agree to the requirements of the study
Active duty special operation forces’ (SOF) personnel stationed at the Fort Campbell, KY military site	SOF personnel are the focus of this study. Fort Campbell is the study site
Exclusion criteria	
Pain intensity ≥4 (using the National Institutes of Health’s PROMIS – question #29) at the initial visit	High pain levels have the potential to confound study results
Additional diagnostic procedure (other than X-ray) or referral required to determine a diagnosis, obtain a second opinion, or to manage a condition	Additional clinical diagnostic procedures are beyond the scope of this study
Bone and joint pathology contraindications for chiropractic manipulative therapy (CMT). Potential participants with conditions such as recent spinal fracture, concurrent spinal or paraspinal tumor(s), spinal or paraspinal infection(s), inflammatory arthropathies and significant osteoporosis	Participant safety. Care outside study scope needed
Other contraindications for CMT or suspicion of such contraindication requiring a consultation with another provider (i.e., unstable spinal segments, suspected cauda equina syndrome)	Participant safety. Care outside study scope needed
Currently being treated for traumatic brain injury	Potential to confound study results
No known or pending deployment, orders for a distant duty assignment or training site, or other absence from the current military site during the study participation period (2–4 weeks)	Compromises ability to adhere to study protocol
Received care from a doctor of chiropractic within the past 30 days	Prevent possibility of carryover effects from recent chiropractic care

There have been two changes in the eligibility criteria since this study began. Originally, the upper age limit was set at 45 years. However, as recruitment progressed it became apparent that SOF included members over the original age limit with an interest in the study. Consequently, it was decided to allow those who were still active in SOF to participate with no upper age limit. The second change allowed women to participate in the study. Initial study recruitment was limited to personnel who were not only in SOF, but were also special forces-qualified – a subset of SOF personnel who could not be female. In order to meet the required rate of recruitment, it was necessary to broaden the scope of eligibility to include members of the Special Operations Aviation Regiment who are on flight status, which includes female pilots. Both changes were approved by all IRBs involved in this study. The changes were made after 41 participants had been enrolled in the study.

### Between visit 1 and visit 2

The data from visit 1 is entered into STaRS. If all eligibility criteria are met, the participant is randomly allocated to either the treatment group or the wait-list control group. Group assignment is done using concealed allocation in a 1:1 ratio by a predetermined, computer-generated, restricted randomization scheme with random block sizes of 2, 4 or 6. The site PM has no knowledge of any details of the randomization process but accesses the group allocation module within STaRS to retrieve the participant ID and assigned group. The group assignment and date, time, and study participant ID are stored in the Structured Query Language (SQL) database. If the STaRS database is unable to be accessed when a participant needs to be allocated to a group, there is a backup allocation protocol consisting of predetermined sequentially numbered, opaque envelopes. Once allocation has been made to either the treatment group or the wait-list control group, the participant is called or sent a text message specifying their group assignment. Personnel at the PCCR who process the raw data are blinded to which group individual participants have been allocated to and will remain blinded until after completion of the study.

### Study interventions

The criteria for determining the clinical appropriateness for CMT are similar for the minimally symptomatic (current pain intensity no more than 4/10) and the totally asymptomatic participants of this study. The DCs perform a clinical evaluation, which may include standard orthopedic tests, spinal ranges-of-motion assessments, gross movement patterns, paraspinal muscular evaluation, and spine-related palpatory examinations to identify areas that may respond to CMT. Clinicians may use findings such as point tenderness over the spine, local muscular hypertonicity, asymmetry in posture, or pain/tenderness produced with orthopedic examination maneuvers to provide information regarding the appropriateness of spinal manipulation. In this manner, clinical evaluation can reveal musculoskeletal dysfunction in otherwise asymptomatic patients.

When applicable, the DCs decide which specific form of CMT to use based primarily upon the diagnosis and combination of comorbid or complicating diagnoses, if any. The participant’s previous response to care (if known), flexibility and mobility, and general condition are also considered. The study chiropractor then makes a second decision regarding the application (location and direction) of CMT to the spine. This decision is based upon the diagnosis and other examination findings such as tenderness, hypertonicity, hypomobility, positions of relief and provocation, imaging findings (e.g., spinal curvatures, degeneration, spondylolisthesis) and other factors individual to the case. The care given to any individual participant consists of high-velocity low-amplitude (HVLA) spinal manipulative procedures. These procedures are typically associated with a quick manual thrust and an accompanying cavitation sound. For the cervical spine, the DCs use a cervical diversified technique. Thoracic manipulation occurs with unilateral or bimanual contacts in the prone or supine positions. Lumbar/pelvis manipulation is performed with a procedure referred to as side-lying or side-posture.

### Visit 2

At visit 2, the site PM shows the same instructional videos that were seen at visit 1 to the participant just before the participant performs the biomechanical tests. The participants are first asked to complete two repetitions of each of the five biomechanical tests. Following the two repetitions of the five tests, those in the treatment group receive their first CMT. Those in the wait-list control group wait for 10 min, the typical amount of time for a CMT to be given. Participants of both groups then complete one more repetition of each of the five biomechanical tests.

### Visits 3 and 4

Participants in the treatment group come in for two more visits and receive CMT over the next week with no biomechanical assessments. Participants in the wait-list control group do not attend these visits.

### Final visit

The final visit of the study is the fifth visit for those in the treatment group and the third visit for those in the wait-list control group. At the beginning of this visit, the participant logs into STaRS and completes the health care utilization and medication-use form and the PROMIS-29 questionnaire, as was also done during visit 1. The five biomechanical tests and CMT/break are conducted in the same manner as at visit 2, which marks the completion of an individual’s participation in the study. Those who are in the wait-list control group are then offered the opportunity to receive CMT. If desired by the participant, the first of four CMTs is given at the final visit of their participation in the study after completion of the biomechanical tests.

### Missed visits

Due to the nature of SOF missions, unexpected deployments or local mission essential requirements can occur. Consequently, there are times when participants are not able to complete the study visits within the normal 2-week time window. However, participants must complete each of the visits for the study in the prescribed sequence. In the event of a missed appointment, the site PM contacts the participant to reschedule. It the study visits cannot be completed within 4 weeks, the PI and site PM discuss additional scheduling options on a case-by-case basis. If all visits are unable to be completed, the participant is considered as lost-to-follow-up.

### Outcome measures

Reaction times are typically very quick (less than 1 s). Subsequent changes in reaction time would be shorter still. Consequently, any tests to be used in this study must be very precise. Reaction time is the time from when a prompt is presented to the beginning of movement in response to that prompt. Response time is the time from when a prompt is given to the completion of a specified task. Three outcome measures are used that involve only a slight degree of movement, so the response time is essentially the same as the reaction time. Two additional outcome measures involve a higher degree of motion and require a longer period of time from the prompt to the response completion. Therefore, the length of time required to complete those tasks is more accurately referred to as response time. However, the movement required for these two outcome measures is still quite small – the response time for each event is still usually less than 1 s.

Before data collection was initiated at Fort Campbell, a pilot study was conducted at Palmer College of Chiropractic to develop and refine the specific procedures for each outcome measure. The three reaction time tests and two response time tests used in this study are described below. Due to the lack of information in the literature concerning these five biomechanical tests, no specific one of the five tests was selected as a primary outcome measure.

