### Statistical methods

An intention-to-treat approach, in which participants will be analyzed according to their original treatment allocation, will be used. All observed data will be used in the analyses. Data analyses will be performed using SAS. The level of significance will be set at 0.05. Descriptive statistics of participant baseline characteristics, the reaction and response times and the PROMIS-29 scales at visit 1 will be presented for each treatment group.

The primary analyses compare the mean changes in reaction and response times from sequence A, performed before CMT/break at visit 2, to sequence A performed before CMT/break at the final visit between the treatment and wait-list control groups, using an analysis of covariance controlling for age, for each of the five biomechanical tests. Residual plots will be used to assess the validity of the model assumptions. If group variances are heterogeneous, we will use a mixed-effects regression model. If the data is non-normal, we will explore data transformations. Mean differences between groups, adjusted for age, will be reported with 95 % confidence intervals.

The secondary analyses will compare the immediate changes in sequence A before CMT/break to sequence A after CMT/break at both visit 2 and the final visit using the same methods described above.

Although we do not expect changes in the PROMIS-29 Health Survey scales or medication use in this short time frame, we will explore it by analyzing changes from visit 1 to the final visit.

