### Sample size

A power analysis used the standard deviations of mean changes in response/reaction time over a 1-week period for each of the five biomechanical variables obtained in the pilot study. We estimated effect size as a 10 % change of the mean response/reaction time measured at visit 1 for each variable, assuming the control group would have no change. A total sample size of 100 participants, with 50 per group, gives at least 85 % power to detect a 10 % difference in mean change between groups at a 0.05 level of significance. We increased the sample size to 120, with 60 per group, to account for the possibility of up to 15 % loss-to-follow-up.

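### Five primary tests each at 0.05, with no adjustment or claim rule: if any one suffices, family-wise error is about 15–23% in either direction, about 7–12% in favour of CMT

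*Protocol article*

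**What the plan says.** All of this is in the protocol article.

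- **Hypothesis (Background).** The objective is to "test the hypothesis that CMT improves the reaction and response times of these highly motivated and extremely physically fit individuals". It is one directional statement about reaction and response times together.
- **Outcome measures.** Because the literature offered little guidance on the five tests, "no specific one of the five tests was selected as a primary outcome measure".
- **Primary analyses (Statistical methods).** The change from visit 2 to the final visit, on the sequence-A repetition done before CMT or break, is compared between groups "using an analysis of covariance controlling for age, for each of the five biomechanical tests". The same section states: "The level of significance will be set at 0.05". Sidedness is not given, but "Mean differences between groups, adjusted for age, will be reported with 95 % confidence intervals".
- **Secondary analyses (Statistical methods).** Immediate change across the CMT or break is analysed by the same methods at visit 2 and at the final visit, for each of the five tests.
- **Sample size.** Effect size is set per variable: "We estimated effect size as a 10 % change of the mean response/reaction time measured at visit 1 for each variable". Fifty per group "gives at least 85 % power to detect a 10 % difference in mean change between groups at a 0.05 level of significance"; enrolment is raised to 60 per group for up to 15% loss.

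The article describes no multiplicity adjustment, testing order, global test or rule for how many of the five must be positive. The limitations section does not raise the subject.

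**The concern.** A single hypothesis is tested five times, each time as a primary analysis at the full 0.05. The article does not say what pattern of results would count as support. It could be any one test, most of them or all five. That choice can therefore be made after the results are known, and the error rate of the trial's main claim depends on it. Under the most permissive choice, any one of five, 0.05 is the error rate of each comparison but not of the claim.

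The power statement has the same limit. It describes one test at unadjusted 0.05, so it would not describe a primary analysis that controlled the error across the five.

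At stake is whether an isolated positive result on one test could be presented as showing that CMT improves reaction and response times, with nothing in the plan to prevent it.

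**Working it through.** **Inputs from the article:** 5 primary comparisons; significance level 0.05, undivided; power of at least 85% with 50 per group at 0.05; 60 per group enrolled; up to 15% loss.

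**Assumptions:** two-sided tests (inferred from the 95% intervals); a common correlation ρ between the five test statistics, varied from 0 to 0.7 because the article gives none; a claim made if any one test is significant.

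**1. The plan's own figures.** The 85% cannot be reproduced, because the pilot means and standard deviations are not given. The standardised difference it implies can be back-solved with the normal approximation:

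d = (1.960 + 1.036) × √(2/50) = 2.996 × 0.2 ≈ 0.60

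The inflation step does reproduce: 100/0.85 = 117.6, so 118, against 120 stated.

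**2. Family-wise error, independent tests.**

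- Either direction: 1 − 0.95⁵ = 0.226, against 0.05 for one test.
- In favour of CMT only: 1 − 0.975⁵ = 0.119, against 0.025 for one test.

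**3. Family-wise error, correlated tests.** With equicorrelated normal statistics and c = 1.960, the error is 1 − ∫ p(u)⁵ φ(u) du. For either direction, p(u) = Φ((c − √ρ·u)/√(1−ρ)) − Φ((−c − √ρ·u)/√(1−ρ)). For the favourable direction only, the second term is dropped.

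| ρ | Either direction | Favouring CMT |
|---|---|---|
| 0 | 22.6% | 11.9% |
| 0.3 | 20.9% | 10.5% |
| 0.5 | 18.3% | 9.1% |
| 0.7 | 14.8% | 7.4% |
| One test alone | 5% | 2.5% |

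**4. Dependence on the claim rule.** If at least two favourable results were required, the chance of a false claim would be about 0.6% (ρ = 0) to 2.9% (ρ = 0.7). If all five had to be significant, it could not exceed 5%. The inflation therefore belongs to the any-one-of-five rule, which the article neither adopts nor excludes.

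**5. Error after adjustment.** Holm's first step is 0.05/5 = 0.01. With all five nulls true and independent, the family-wise error is 1 − 0.99⁵ = 4.9% in either direction, and 1 − 0.995⁵ = 2.5% favouring CMT.

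**6. Power at 0.01 (illustration).** Take a test with exactly 85% power at 50 per group:

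- 50 per group: Φ(2.996 − 2.576) = Φ(0.420) ≈ 66%.
- 60 per group: Φ(2.996 × √(60/50) − 2.576) = Φ(0.706) ≈ 76%.

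A test that started at 95% would keep Φ(1.960 + 1.645 − 2.576) = Φ(1.029) ≈ 85%.

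**7. Power of Holm if all five effects are real at that same size (simulation, 50 per group).**

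| ρ | Average power per test | Power for at least one |
|---|---|---|
| 0 | 78% | more than 99% |
| 0.5 | 76% | 93% |
| 0.7 | 75% | 88% |

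**The case against.** The strongest reply is that the any-one-of-five rule is not in the article. Each test is to be reported with its own estimate and interval, and the hypothesis speaks of times in the plural. If claims are made test by test, 0.05 is the correct error rate for each of them. This stands, and it is why every family-wise figure here is conditional. It does not remove the point, because the article states one overall hypothesis and leaves the rule open.

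A second reply is that a statistical analysis plan, not shown, may contain the adjustment. It may. But the article itself fixes the five primary analyses, the undivided 0.05 and the level used for power, and it explains why no test was singled out. If an adjustment exists elsewhere, the 0.05 and the power stated here do not describe the primary analysis and need restating. The lack of literature explains why no test was chosen; it does not justify five unadjusted ones, since Holm needs no prior view on which test will respond.

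A reader might also infer more than the article supports:

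- **That 15–23% is the chance of falsely claiming that CMT speeds reactions.** It also counts false findings that CMT slows them. The favourable part is 7–12%, against 2.5%.
- **That the error is 54%**, from 1 − 0.95¹⁵ over the five primary and ten immediate-change comparisons. The article already labels those ten secondary and sets up no 15-test confirmatory family.
- **That lack of blinding aggravates the problem.** Expectation effects are bias, which no multiplicity procedure removes, and the article discloses the unblinded assessor and the wait-list control as limitations.
- **That the trial's power is really 66%.** The stated 85% is a floor across five variables, and without the pilot standard deviations no test's actual power is known.

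Finally, every interval will be reported, so selective emphasis would be visible. That softens the consequence but leaves the claim rule open.

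**Conclusion.** The point holds in a conditional form. The article fixes five primary comparisons for one hypothesis, each tested and powered at 0.05, and does not say how they combine into a conclusion. If any one significant result is taken as support, the family-wise error is about three to four and a half times nominal (14.8/5 ≈ 3.0; 22.6/5 ≈ 4.5). For a false result favouring CMT the factor is about 3.0 to 4.8 (7.4/2.5; 11.9/2.5).

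The lower ends rest on an assumed correlation of 0.7, the upper ends on independence, and all of them on two-sided testing. Under a stricter claim rule the excess disappears. The power figures at 0.01 are illustrations from a back-solved effect size, not estimates for this trial.

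**What to change.** Before unblinding:

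1. Declare the five changes from visit 2 to the final visit (sequence A, before CMT or break) one primary family. Apply Holm at two-sided 0.05, and claim improvement only for the tests that survive. A single named primary test, a fixed testing order or a global test would also control the error. Holm suits the stated lack of grounds for preferring any one test.
2. Keep the immediate-change analyses as supportive, reported as estimates with 95% confidence intervals.
3. State that the power of at least 85% is per test at unadjusted 0.05, and recompute it for each variable from the pilot standard deviations at the adjusted level. The illustration above (about 66% at 50 per group, about 76% at 60, for a test starting at exactly 85%) shows the possible loss but should not be written into the plan as the trial's power.

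The cost is plan wording and a few lines of code. The downside is a stricter threshold and a lower stated power. The Trial status section says data collection is complete, so the sample size cannot be raised to compensate. The Methods say that those processing the raw data stay blinded until the study is complete, so the change may still be possible in time.
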